## Abstract

**Background:**

The mean incidence of ovarian metastases (OM) in patients with colorectal cancer (CRC) is 3.4%. The 5-year survival of these patients, even when operated with curative intent, is remarkably low. The lifetime risk of ovarian cancer is approximately 1.3%. Prophylactic salpingo-oophorectomy (PSO, or surgical removal of the ovaries and fallopian tubes) could reduce the number of CRC patients that develop OM after removal of the primary tumor, as well as preventing the occurrence of primary ovarian cancer. Recently, the care pathway for CRC has been changed in several hospitals in line with the updated Dutch guideline. The possibility of PSO is now discussed with postmenopausal CRC patients in these hospitals. The aims of the current study are firstly to estimate the incidence of OM and primary ovarian cancer in postmenopausal patients with CRC, and secondly to evaluate the effect of PSO in these patients.

**Methods:**

An information bulletin and decision guide on this topic was implemented in several Dutch hospitals in 2020. Post-decision outcomes will be collected prospectively. The study population consists of postmenopausal (≥ 60 years of age) patients that are operated with curative intent for CRC. Based on their own preference, patients will be divided into two groups: those who choose to undergo PSO and those who do not. The main study parameters are the reduction in incidence of ovarian malignancies (metastatic or primary) following PSO, and the number needed to treat (NNT) by PSO to prevent one case of ovarian malignancy.

**Discussion:**

This will be the first study to evaluate the effect of PSO in postmenopausal CRC patients that is facilitated by an altered CRC care pathway. The results of this study are expected to provide relevant information on whether PSO adds significant value to postmenopausal patients with CRC.

**Trial registration:**

International Clinical Trials Registry Platform, NL7870. Registered on 2019 July 12. URL of trial registry record: https://trialsearch.who.int/Trial2.aspx?TrialID=NL7870.

Protocol version: 1.0, date 2021 June 8.

**Supplementary Information:**

The online version contains supplementary material available at 10.1186/s12905-022-02040-1.

## Introduction

Intra-abdominal relapse of colorectal cancer (CRC), including ovarian metastases (OM), is a serious event leading to high morbidity and mortality and to a significant loss in quality of life [1, 2]. For CRC patients with OM, including those who are operated with curative intent, the reported median survival is between 12–18 months [1, 3–5] and the 5-year survival rate is about 12–27% [2, 6–10].

### Occurrence of ovarian metastases

The risk of developing OM in patients with CRC has been reported as between 1–8% [1, 3–5, 8, 11–16], with postmortem studies showing a higher incidence of 5–10% [2]. Review of the literature by Pitt et al. [17] revealed the mean risk for development of synchronous and metachronous OM is 3.4%. The risk of developing OM is considerably higher in young or premenopausal patients, with a mean incidence of 5% (range 3 to 50%) [1, 7, 12, 18–21]. 

### Guideline, evidence for prophylactic surgery, and current practice

The Dutch guideline for CRC management was updated in 2019 and includes discussing the role of prophylactic salpingo-oophorectomy (PSO) to reduce the risk of developing OM and primary ovarian cancer in *postmenopausal* patients [22].

To date, only one randomized controlled study (*n* = *155*) has investigated the impact of prophylactic surgery by randomizing patients into one of two groups: prophylactic oophorectomy or non-oophorectomy [11]. This study found no significant difference between the two groups in terms of disease-free survival at 5 years: 78% for the prophylactic oophorectomy group versus 68% for the non-oophorectomy group (*p* = *0.16*). Furthermore, no significant difference in overall survival was found between the two groups (*p* = *0.7*9). However, the statistical power of this study was quite low and hence no firm conclusions could be drawn.

In accordance with the updated Dutch guideline, PSO is now regularly discussed with postmenopausal (≥ 60 years of age) CRC patients in several Dutch hospitals.

### Consequences of PSO

The removal of ovaries in postmenopausal patients can affect the hormone balance. Following oophorectomy, the concentrations of androstenedione and testosterone decrease by 50%, but this does not lead to significant clinical complaints [23, 24]. A recent study showed that postmenopausal status was a risk factor for the development of CRC and adenomas, due mainly to the production of androgens by the ovaries [25]. This hormonal influence may be the reason why CRC is more prevalent in males, with a male-to-female incidence ratio of 4:3 [26].

The removal of ovaries in postmenopausal patients has several potential disadvantages:1) introduction of extra risk during operation, including bleeding or damage to nearby structures such as ureters. However, this risk appears to be low according to a number of mainly gynecological-focused studies [27–29],2) decreased satisfaction with sexual functioning [30].

Proposed benefits of PSO include [31]:1) resection of microscopic ovarian metastases,2) reduced risk of disease recurrence,3) prevention of primary ovarian cancer, which has a lifetime risk of approximately 1.3% in the general population [32].

### Explanation for the choice of comparators and efficacy of PSO

The primary goal of implementing PSO is to improve the health of individual women by preventing the development of ovarian malignancies (primary or metastatic), thus improving disease-free survival, preventing additional treatment-related morbidity, and ultimately improving overall survival. As such, PSO could potentially be a cost-effective procedure, especially from an oncological point of view [26].

Fear of cancer recurrence is an important issue for CRC survivors [33]. A patients’ ability to choose additional prophylactic surgery could be helpful in reducing their fear, since the risk of subsequent metastatic or primary ovarian cancer is removed. Moreover, this supports the practice of “shared decision making”. Beginning in 2020, counseling for PSO (preference of “yes” or “no” to PSO) started to be implemented in the CRC care pathway in several Dutch hospitals. Consequently, the impact of PSO can be prospectively evaluated.

#### Protocol items

The protocol has been written following the Standard Protocol Items: Recommendations for Interventional Trials (SPIRIT) guidance [34]

## Objectives and outcomes (Table 1)

**Table 1 Tab1:** Primary and secondary outcomes of the study

Outcome	Metric	Time point/period
**Primary**		
Occurrence of ovarian cancer (primary or metastatic)	Incidence	36 months
Number needed to treat to prevent one case of ovarian cancer (primary or metastatic)	NNT	36 months
**Secondary**		
Disease-free survival	DFS	36 months
Number needed to treat with PSO to prevent one case of ovarian cancer (primary or metastatic)	NNT	36 months
Surgery-related morbidity of PSO	Number	36 months
Subsequent intra-abdominal relapse pattern in the non-PSO group	Number	36 months
Abnormal ovaries found during surgery	Number	During surgery
Incidence of ovarian (micro)metastatic disease	Incidence	36 months
Quality of life (EORT QLQ-C30 and EORTC QLQ-CR29)	SUM score	Baseline, 3-, 12-, 24- and 36 months
Repeat surgery for complications (i.e. adhesions)	Numbers	36 months
Long-term overall survival	OS in days	60 months
Preference for PSO	Numbers	36 months
Reversal of decision	Numbers	36 months
Baseline characteristics	Numbers	Before surgery
**Other parameters**		
Type of surgery	Number per type of surgery	During surgery
Operation duration	Minutes	During surgery
Blood loss	Milliliters	During surgery
Pre- and postoperative treatment strategies	Number per type of treatment strategy	Before surgery and 36 months

*NNT* Number needed to treat, *DFS* Disease free survival, *SUM* Single Usability Metric, *OS* Overall survival, *PSO* Prophylactic salpingo-oophorectomy, *EORT QLQ* European Organization for Research and Treatment of Cancer European Union Quality of Life Questionnaire

### Primary objective

The main aim of this study is to determine whether prophylactic bilateral salpingo-oophorectomy conducted in postmenopausal patients aged ≥60 years during surgery for primary CRC reduces the incidence of ovarian malignancies (metastatic or primary) during a three-year follow-up period. Moreover, this study will provide the data necessary to calculate the number needed to treat (NNT) in order to prevent one case of ovarian cancer (metastatic or primary).

### Secondary objectives

• What is the effect of PSO on disease-free survival (DFS) after 3-years of follow-up? What is the concomitant NNT to gain one year of DFS, according to the method of Lubsen *et al.* [35]?• What is the effect of PSO on surgery-related morbidity?• In the non-PSO group, what is the incidence and pattern of intra-abdominal relapse, including CRC ovarian metastases and primary ovarian cancer, requiring renewed surgical intervention?• During primary surgery, how often are abnormal ovaries found that require resection?• What is the incidence of (micro)metastatic disease in the ovaries of patients with primary CRC?• What is the effect of PSO on quality of life as assessed using health-related quality of life (HRQL) questionnaires, and effects such as surgery for abdominal adhesions occurring within 3 years?• What is the effect of PSO on 5-year overall survival?• What is the percentage of patients who have a preference for PSO (or no PSO) when scheduled for surgery for primary CRC? Within 3 years of their index surgery, how many patients revise their initial decision of no PSO and subsequently undergo PSO?• Are there differences in the baseline characteristics between patients who choose PSO compared to those who do not? (The baseline patient characteristics include age, ASA-classification, BMI, previous unilateral oophorectomy, comorbidities, and neo-adjuvant therapy (Table 2))

**Table 2 Tab2:** Baseline characteristics of study patients

Baseline characteristic	PSO	Non-PSO
Age, mean (SD) or median (IQR), years		
ASA classification, No. (%)		
ASA-1		
ASA-2		
ASA-3		
ASA-4		
BMI, mean (SD), median (IQR), kg/m^2^		
Previous (unilateral) oophorectomy		
Yes, unilateral		
Yes, bilateral		
No		
Comorbidities, No. (%)		
Smoking (yes/no)		
Chronic pulmonary disease (yes/no)		
Hypertension (yes/no)		
Diabetes mellitus (yes/no)		
Myocardial infarction (yes/no)		
Transient ischemic attack (yes/no)		
Cerebral vascular accident (yes/no)		
Central arterial disease (yes/no)		
Peripheral arterial disease (yes/no)		
Severe kidney disease (GFR < 30 mg/mmol) (yes/no)		
Neo-adjuvant therapy		
No		
Yes, chemotherapy		
Yes, radiotherapy		
Yes, chemoradiotherapy		

*SD* standard deviation, *IQR* interquartile range, *y* year, *ASA* American society of anesthesiologists, *no* number, *BMI* body mass index, *GFR* glomerular filtration rate

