### Current practice and study setting

In 2020 an information bulletin and decision guide (Additional file 1) on PSO was implemented in several Dutch hospitals for female patients ≥ 60 years of age. In patients that opted for PSO, prophylactic surgery during CRC will be performed by surgeons, gynecologists, or both (depending on the surgeons’ experience and local hospital policies).

Post-decision outcomes are collected prospectively with standardized variables and data are stored in electronic patient files. These variables will be used for various statistical analyses and will provide evidence as to whether or not PSO adds significant value to postmenopausal CRC patients.

The following website lists all hospitals that contributed patients to this study: https://romic.surgery/ziekenhuizen/.

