### Study population and eligibility criteria

All female patients with CRC who received the information bulletin and decision guide and who signed informed consent (IC) for use of follow-up data are included in this study cohort. Patients are also included when they answered positively to the ‘opt-in’ question for research and education within their electronic health record. Figure 1 shows schematic representation of the study cohort.

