#### Inclusion criteria

• Female sex• Age ≥60 years at the time of CRC diagnosis• Intended curative resection of colon or rectal cancer, with no evidence of incurable distant metastases• Informed consent (Additional file 2) or consent by opt-in form (for research and education)

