#### Exclusion criteria

• No signed informed consent and no consent by opt-in form (for research and education)• Surgery with palliative intent• Known distant metastases preoperatively, or evidence of distant or intraperitoneal metastases during operation, except when curative metastasectomy is considered possible (e.g. for hepatic metastases)

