### Sample size

The primary study outcome is the occurrence of either CRC metastases in the ovaries or primary ovarian cancer within 3 years after resection of the (primary) colorectal tumor. Based on previous studies, we assume the incidence of synchronous and metachronous colorectal metastases in the ovaries will be 2.0% during the follow-up period [15, 17, 21]. The incidence of primary ovarian cancer is expected to be 0.1% in this period [39]. This gives an overall incidence of 2.1% in cases where PSO is not performed (non-PSO group).

Following PSO, colorectal tumors can no longer metastasize to the ovaries, while the incidence of primary ovarian malignancy should presumably be 0% (PSO group). However, a small risk of primary ovarian malignancy still exists after PSO due to the development of ‘ovarian remnant syndrome’ (ORS) [40–42]. This risk is estimated to be approximately 0.01% for the PSO group.

Based on these assumptions and an alfa of 0.05 with power of 80%, a sample size calculation was performed using an online sample size calculator for comparison of two proportions [43]. This gave a sample size of 371 patients per group, or 742 in total.

Since all eligible patients are not randomized, it is necessary to correct for possible confounders. According to the one-in-ten rule, at least 10 events (of ovarian malignancies) are needed per factor studied in order to achieve sufficient statistical power [44]. Besides PSO, correction will also be made for age as another possible confounder.

Based on current clinical practice, we estimate that about half of all postmenopausal CRC patients undergo PSO during resection of their colorectal tumor. Therefore, we expect the two study groups to be approximately equal in size. The estimated incidence of ovarian malignancies in the total study population will thus be 1.055% (average of 2.1% and 0.01%), thus requiring a sample size of at least 1896 patients (20/0.01055).

Finally, after taking into account a dropout rate of 5%, at least 1996 patients should be recruited into the study.

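### Eligibility does not require an ovary in place: a woman with a previous bilateral oophorectomy could enter, and only as a non-PSO patient, which lowers the non-PSO incidence and inflates the NNT

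*Protocol article*

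**What the plan says.** - **Who receives the decision guide** (Current practice and study setting): it "was implemented in several Dutch hospitals for female patients ≥ 60 years of age". No ovarian-status condition is given.
- **Study population** (Study population and eligibility criteria): "All female patients with CRC who received the information bulletin and decision guide" and who consented.
- **Inclusion criteria:** female sex, age 60 or over, consent, and "Intended curative resection of colon or rectal cancer, with no evidence of incurable distant metastases".
- **Exclusion criteria:** lack of consent, "Surgery with palliative intent", and distant or intraperitoneal metastases that are not considered curable. Previous bilateral oophorectomy is not listed.
- **Baseline variables** (Secondary objectives): the text names "previous unilateral oophorectomy, comorbidities, and neo-adjuvant therapy (Table 2". The matching variable in Table 2 has unilateral in brackets in its heading, yet its rows include "Yes, bilateral", under both a PSO and a non-PSO column.
- **Cohorts** (Methods/design): cohort 1 is everyone who had PSO, and cohort 2 is everyone who did not choose it.
- **Outcomes** (Table 1): the incidence of ovarian malignancy and the NNT to prevent one case, both at 36 months, are primary. Preference for PSO is secondary.
- **Sample size:** 2.1% is assumed without PSO (2.0% metastases plus 0.1% primary cancer) and 0.01% with PSO.

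**The concern.** A woman whose ovaries have already been removed cannot undergo PSO. If she is enrolled, the cohort definitions place her in cohort 2. For the primary outcome she resembles a PSO patient, but she is counted as a control.

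All such women fall on one side of the comparison, so the direction of the bias is known. The non-PSO incidence goes down, the risk difference shrinks and the NNT goes up. An NNT for an operation has meaning only among women who can have that operation. The percentage preferring PSO would also include women who had nothing to decide.

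Nothing under Statistical methods sets these women aside for the crude incidence or the NNT. The same section does set aside another group, women whose ovaries look abnormal at surgery, for separate analysis.

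**Working it through.** **Inputs (Sample size section).** Non-PSO incidence p1 = 0.021; PSO incidence p2 = 0.0001; alpha 0.05, taken as two-sided; power 80%; groups about equal; 20 events wanted (10 each for PSO and age); dropout 5%.

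**The plan's own figures reproduce.**
- Per group, unpooled variance: (1.96 + 0.8416)² × (0.021 × 0.979 + 0.0001 × 0.9999) / 0.0209² = 371.2, against the stated 371. Pooled variance gives 374.
- Average incidence: (0.021 + 0.0001)/2 = 0.01055. N for 20 events: 20/0.01055 = 1895.7, so 1896.
- Dropout: 1896/0.95 = 1995.8, so 1996.
- Implied NNT, as the reciprocal of the risk difference: 1/(0.021 − 0.0001) = 47.8.

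**Dilution.** Let f be the share of the non-PSO group with no ovaries. The protocol gives no value, so f is an assumption shown over a range. A second assumption is that 2.1% is the rate in women with ovaries. With 948 women per group:
- Non-PSO incidence q = 0.021 × (1 − f)
- NNT = 1/(q − 0.0001)
- Expected events in 1896 women = 948 × (q + 0.0001)
- N for 20 events = 40/(q + 0.0001), then divided by 0.95 for dropout

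| f | Incidence q | NNT | Events in 1896 | N for 20 events | After 5% dropout | Power at 948 per group |
|---|---|---|---|---|---|---|
| 0 | 2.10% | 47.8 | 20.0 | 1896 | 1996 | 99.4% |
| 2% | 2.06% | 48.8 | 19.6 | 1935 | 2037 | 99.3% |
| 5% | 2.00% | 50.4 | 19.0 | 1996 | 2102 | 99.2% |
| 10% | 1.89% | 53.2 | 18.0 | 2106 | 2217 | 98.8% |
| 20% | 1.68% | 59.9 | 16.0 | 2367 | 2492 | 97.8% |

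**Which denominator.** Here f is a share of the non-PSO group. Because all affected women fall there, a share of the whole cohort counts about double: 5% of 1896 is 95 women, or 10% of 948. If the remaining 95% split evenly, the non-PSO group is 52.5% of the cohort and f = 0.05/0.525 = 9.5%. The NNT is then 52.9, with 19.0 expected events, close to the 10% row.

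**The case against.** **Such women may never be enrolled.** Methods/design describes patients who were offered the option of PSO, and groups are formed by preference. A woman without ovaries has no such option and may not be handed the guide. The Table 2 heading and the preceding text say unilateral only. The bilateral row also sits in an empty shell with a PSO column, where it is impossible, so it may be a leftover form category. The cohort diagram (Figure 1) and the decision guide (Additional file 1) were not available for this check and may carry a restriction. This stands in part. A reader might infer from Table 2 that these women are expected in the cohort, but the text shows only that they are not kept out.

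**The 2.1% may already include them.** The Sample size section takes its metastasis rate from cited studies and applies it wherever PSO is not performed. It does not say that those studies were limited to women with ovaries. If they were not, some dilution is already in the 2.1%, and the falls tabulated above do not follow as stated. This stands, so the premise is an assumption. It does not change the direction of the bias relative to women who have ovaries.

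**The shift is small against sampling error.** With about 20 control events, exact Poisson 95% limits are roughly 12 to 31 events, an NNT of about 31 to 78 (948/31 to 948/12.2). A shift from 48 to 50 or 53 lies well inside that. This stands as to size, but the bias is systematic and avoidable.

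**Regression would absorb it.** Baseline variables that differ between groups enter the models for disease-free survival, complications, relapse and primary ovarian cancer. This helps those analyses if the bilateral category is coded separately. It does not reach the crude incidence, the NNT or the preference percentage.

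**Conclusion.** The point holds as a gap in the written criteria plus an inconsistency within Secondary objectives and Table 2. Any woman with a previous bilateral oophorectomy who is enrolled counts as non-PSO with essentially no risk of the primary outcome. The direction is certain: lower non-PSO incidence, an effect nearer null and a higher NNT.

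The size is unknown. It rests on an undocumented prevalence and on reading 2.1% as the rate in women with ovaries. At 5% or less of the non-PSO group, the NNT moves by under 3 and the N for 20 events by up to 100. At 20%, the NNT reaches 59.9 and expected events fall to 16.0.

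A reader might infer that the study becomes underpowered, but power of the unadjusted comparison stays at about 97.8% or more. The exposed quantities are the incidence, the NNT and the 20-event target, which has no slack. That target is for both groups together. The non-PSO group alone is expected to give 948 × 0.021 = 19.9 events even without dilution, so a control count below 20 is not in itself a shortfall.

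Severity is minor to moderate, confidence moderate.

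**What to change.** 1. Add previous bilateral (salpingo-)oophorectomy to the exclusion criteria. Women with a previous unilateral oophorectomy still have an ovary at risk and stay in.
2. Keep the ovarian-status field, including its bilateral category, because it is what identifies affected women already enrolled. Remove those women from the PSO versus non-PSO comparisons, from the incidence and NNT denominators and from the preference percentage, and report how many were removed.
3. Reconcile the Table 2 heading, its rows and the list of baseline characteristics in Secondary objectives.

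The cost is one eligibility line and a table correction. The variable is already collected, and the women removed carry no information on what PSO prevents. With them excluded, the stated 2.1%, 1896 and 1996 need no change. Women already enrolled and then removed would have to be replaced to keep 948 evaluable non-PSO patients: f × 948, or about 19, 47, 95 or 190 at 2%, 5%, 10% or 20%.

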### Other study parameters

Other information will be collected on the type of surgery (colon *vs* rectum, laparoscopic *vs* open), operative duration, intraoperative blood loss, adjuvant treatment strategies, and pTNM classification. Preoperative data are collected during admission to the surgical and/or gynecology department. Data collected during operation is noted in the operative report. Quality of life after the operation is evaluated by questionnaires (part of the standard follow-up / value-based healthcare) given at 3 months and at 1-, 2- and 3-year(s) after surgery. Data collection is performed centrally.

